### **Immunogenicity (MS01.03)**

All three dose levels were shown to be immunogenic, with the highest dose being immunogenic in all subjects. In both the  $5 \times 10^7$  and  $5 \times 10^8$  CFU dose groups 9 (56%) subjects in each group mounted an IgA immune response on Day 7 or an IgG response on Day 28. This number increased to 16 (100%) in the  $5 \times 10^9$  CFU dose group. None of the subjects that received placebo mounted an immunological response against *S. typhi* (Ty2 aroC ssaV) ZH9.

### **Summary of Data from Study MS01.04**

Study MS01.04 was a single centre, open, randomised, parallel group study conducted under an IND. The study was designed to determine the immunogenicity and safety of two different presentations of  $5 \times 10^9$  CFU of M01ZH09 administered as a single oral dose to healthy volunteers. A total of 32 healthy adult volunteers were recruited to the study. Sixteen subjects were randomised to receive vaccine presentation 1 and 16 to vaccine presentation 2.

Subjects receiving vaccine presentation 1 consumed 100 mL of 2% (w/v) sodium bicarbonate solution between 5 and 20 minutes prior to receiving the vaccine administered in a further 50 mL of 2% (w/v) sodium bicarbonate solution. The solution was prepared using bottled water.

Subjects randomised to vaccine presentation 2, received the vaccine in 150 mL of a solution containing 1.75% (w/v) sodium bicarbonate, 1.1% (w/v) ascorbic acid and 0.02% (w/v) aspartame. The solution was prepared using tap water.

All 32 subjects who entered the study received their dose of vaccine and 31 subjects completed the study. One subject withdrew their consent and therefore did not complete the study.

#### **Safety Data (MS01.04)**

The majority of subjects (84%) in the study reported at least one post-vaccination adverse event. A total of 15 (94%) of subjects that received M01ZH09 in presentation 1 reported 44 events. In comparison a total of 12 (75%) subjects that received M01ZH09 in presentation 2, reported 51 events. The majority of the events were gastrointestinal or nervous system disorders.

Gastrointestinal disorders were reported by 8 (50%) subjects in each presentation group. The commonest events specific to the gastrointestinal system were loose stools, which were reported by 4 and 2 subjects for presentations 1 and 2 respectively and abdominal pain, which were reported by 3 and 1 subject(s) respectively. Nervous system disorders were reported by 6 (38%) subjects in presentation 1 and by 10 (63%) subjects in presentation 2. The commonest event specific to the nervous system was headache, which was reported by 6 and 9 subjects for presentations 1 and 2 respectively. Respiratory, thoracic and mediastinal disorders were reported by 3 (19%) subjects receiving presentation 1 and 5 (31%) subjects receiving presentation 2.

There were no deaths or SAEs reported. The majority of events were of mild or moderate severity with only 7 of the 95 events being reported as severe.

There was little difference between the presentations in terms of the occurrence of adverse events.

#### **Immunogenicity Data (MS01.04)**

The majority of subjects showed an immune response following administration of M01ZH09. Fifteen subjects (94%) who received presentation 1 mounted an immune response as demonstrated by an increase in the number of antibody secreting cells (ASCs) to 4 or more and /or seroconversion of the subjects with the presence of IgG antibody specific to *S. typhi* LPS. Fourteen subjects (93%) who received presentation 2 mounted an immune response. Both groups had a statistically significant difference to an assumed response rate of 50%, ( $p \leq 0.001$ ; 95% CIs (69.8%, 99.8%) for presentation 1 and (68.1%, 99.8%) for presentation 2).

For the IgG response, the proportion of subjects who had an immune response was higher for presentation 1 (13 subjects, 81%, 95% CI (54.4%, 96.0%)) than for presentation 2 (8 subjects, 53%, 95% CI (26.6%, 78.7%)).

For the IgA response, 14 subjects in both groups mounted an immune response but the proportion of subjects who had an immune response was lower for presentation 1 (14 subjects, 88%, 95% CI (61.7%, 98.4%)) than for presentation 2 (14 subjects, 93%, 95% CI (68.1%, 99.8%)) as one subject in presentation 2 did not attend the Day 7 visit to provide a blood sample.

There was no evidence of a difference between the groups in the proportion of subjects mounting either an IGA or an IGG immune response ( $p=1.0$ ; 95% CI (-16.9%, 17.7%)).

Similar results were seen for the IgA response alone ( $p=1.0$ ; 95% CI (-26.4%, 14.7%)).

For the IgG response there were differences in the proportions of subjects showing an immune response although this difference was not statistically significant ( $p=0.1351$ ; 95% CI (-3.8%, 59.6%)).

Overall the immunogenicity was comparable for both presentations and the safety profiles were similar. Based on these data it seems appropriate to use presentation 2 in MS01.07 as it is prepared and administered in a more convenient way and also the total amount of bicarbonate consumed is lower (2.6g compared to 3g).

### **Summary of Data from Study MS01.07**

Study MS01.07 was a single centre, placebo-controlled, single-blind, randomised, parallel group, single oral dose study. The study was designed to determine the immunogenicity and safety of  $5 \times 10^9$  CFU of M01ZH09 administered as a single oral dose to healthy adult volunteers of Vietnamese origin. The study planned to recruit 28 subjects. A total of 27 healthy adult volunteers were actually recruited to the study. It was anticipated that 16 subjects would be randomised to receive vaccine and 12 subjects to receive placebo. The actual number of subjects that received vaccine was 16 and the number that received placebo was 11.

Subjects received either vaccine or placebo in 150 mL of a buffer solution containing 1.75% (w/v) sodium bicarbonate, 1.1% (w/v) ascorbic acid and 0.02% (w/v) aspartame. The buffer solution was prepared using drinking water.

All 27 subjects that entered the study received their dose of either vaccine or placebo and all 27 completed the study.

### **Safety Data (MS01.07)**

Nine (82%) of the subjects who received placebo reported a total of 14 adverse events and 8 (50%) of subjects that received M01ZH09 reported 23 adverse events. The only events reported by 10% or more of subjects were diarrhoea, abdominal pain and headache. There were no apparent differences between the placebo and active groups in the frequencies of these events.

None of the subjects recorded a bacteraemia, a serious or a severe adverse event and none of the subjects withdrew due to an adverse event. The majority of events were of mild severity with only 5 events considered to be of moderate severity. None of the adverse events reported required treatment or medication for the adverse event.

None of the subjects recorded or reported a fever or had any clinically significant changes in laboratory parameters.

None of the subjects experienced persistent faecal shedding of *S. typhi* (Ty2 *aroC* *ssaV*) ZH9. (Persistent faecal shedding was defined as shedding of *S. typhi* (Ty2 *aroC* *ssaV*) ZH9 beyond day 7).

Overall M01ZH09 appears to have been very well tolerated and to have a good safety profile in healthy adult Vietnamese subjects.

### **Immunogenicity Data (MS01.07)**

Sera from blood were taken fortnightly until Day 28 and will be obtained 6 month post vaccination for the evaluation of IgG responses against *S. typhi* LPS, *S. typhi* flagellin and *S. typhi* Vi as assessed by the ELISA technique. Peripheral blood mononuclear cells (PBMC) were isolated from blood

collected on Days 0 and 7 and assayed, using the ELISPOT technique, for the presence of ASCs secreting IgA specific for *S.typhi* LPS.

Subjects were considered to have had an immune response if they achieved a Day 7 result of  $\geq 4$  ASCs per  $10^6$  PBMC, secreting IgA specific for *S. typhi* LPS detected by ELISPOT assay, (assuming a Day 0 result of  $<4$  ASCs per  $10^6$  PBMC), and/or undergo seroconversion for serum IgG to LPS. Seroconversion for serum IgG to LPS is defined as a four-fold or greater increase in the serum IgG antibody on serial dilution by ELISA, to *S. typhi* LPS between Day 0 and Day 28.

None of the subjects that received the placebo mounted an immunological response against *S.typhi* (Ty2 *aroC* *ssaV*) ZH9. 11/15 subjects (73%) within the group receiving a single dose ( $5 \times 10^9$  CFU) of M01ZH09 typhoid vaccine demonstrated an LPS specific IgA response between day 0 and day 7. 3/16 subjects (19%) demonstrated an LPS specific IgG response between day 0 and day 28.

Overall 69% (11/16) of subjects within the group receiving a single dose ( $5 \times 10^9$  CFU) of *S.typhi* (Ty2 *aroC* *ssaV*) ZH9 satisfied the primary immunogenicity endpoint of the MS01.07 study (ITT population).

## 2.5 Rationale for Dose

The purpose of this study is to investigate the safety and immunogenicity of the vaccine in a different age group to that tested to date. To achieve this it is essential to use a dose that is known to be immunogenic. In study MS01.03 the maximum dose administered ( $5 \times 10^9$  CFU) was immunogenic in all 16 subjects dosed. The lower doses investigated in Study MS01.03 were immunogenic in approximately 50% of the subjects. The safety profiles were similar for all groups; hence, at the doses investigated toxicity did not limit dosing. In Study MS01.04, the dose studied ( $5 \times 10^9$  CFU) was immunogenic in 29 of 32 subjects. In Study MS01.07, the dose studied ( $5 \times 10^9$  CFU) was immunogenic in 11 of 16 Vietnamese subjects. There is precedent for using the same dosage of live typhoid vaccine in children as adults. School children in the Vivotif (Ty21a) clinical trial in Chile received the same regimen as used for the licensed product in adults (Ferreccio et al., 1989). Moreover, Vivotif is licensed for use in the US; it is indicated for immunisation of adults and children greater than 6 years of age using the same immunisation schedule. In line with other live vaccines, such as Stamaril (yellow fever) and Meruvax II (rubella), the same parenteral dose is given to children as it is to adults. For these reasons it has been determined that the appropriate dose for this study is a nominal dose of  $5 \times 10^9$  CFU of *S. typhi* (Ty2 *aroC* *ssaV*) ZH9.

## 2.6 Study Population

The study will recruit 150 healthy paediatric Vietnamese subjects. Subjects will be of either gender and will be between 5 and 14 years of age, who are willing to take part, whose parents or guardians give written permission and who meet all the inclusion and exclusion criteria.

At least 70% of the subjects in each group will be aged 5 to 10 years inclusive.

## 2.7 Risks and Benefits

The anticipated risks of the study are in line with the side effect profile seen to date with M01ZH09. The most likely adverse effects are flatulence, abdominal cramps/discomfort, loose/unformed

stools, headache, nausea, vomiting, chills/rigors, minor elevations in body temperature (up to 38°C) and mild muscle and joint pain in subjects receiving the active vaccine.

For subjects receiving the active vaccine there is a theoretical risk of developing a mild typhoid-like condition. Theoretically there is also a potential risk of subjects developing a clinically significant bacteraemia, or becoming a carrier of the *Salmonella* strain *S. typhi* (Ty2 aroC ssaV) ZH9, and while these outcomes are considered highly unlikely and have not been seen to date in the populations studied, both these conditions would require treatment with antibiotics (refer to Section 6.6 for recommended antibiotic treatment).

There is a potential risk of subjects developing allergic symptoms, such as rashes or anaphylaxis. There may also be other as yet unforeseen risks.

The investigational product will be administered in a bicarbonate solution containing 1.75% (w/v) sodium bicarbonate, 1.1% (w/v) ascorbic acid and 0.02% (w/v) aspartame. Subjects aged 5 to 10 years will receive the vaccine or placebo in 75 mL of bicarbonate solution. Subjects aged 11 to 14 years will receive the vaccine or placebo in 150 mL of bicarbonate solution. The solution is prepared from effervescent bicarbonate tablets using drinking water. The bicarbonate solution may induce some abdominal discomfort and/or cramping around the time of dosing.

Subjects who have received  $5 \times 10^9$  CFU of M01ZH09 have developed an immune response. At present it is not known if the immune response generated by M01ZH09 is protective against infection from *S. typhi*. There can be no assumed benefit for the subjects receiving M01ZH09 even if an immune response is detected; such a response cannot be assumed to be protective. If any protection is obtained, the duration of any such protection is currently unknown.

## 2.8 Study Treatment

Subjects will receive a single dose of M01ZH09 administered orally. The oral route of administration is the normal route of entry for *S. typhi* hence it is appropriate to administer the vaccine by the same route. There will be 2 groups of subjects; 100 subjects will be randomised to receive a nominal dose of  $5 \times 10^9$  CFU of M01ZH09 oral vaccine and 50 subjects will receive placebo. M01ZH09 is supplied as a freeze-dried formulation of the vaccine strain, plus excipients, in single dose vials. The placebo is supplied as a freeze-dried formulation of vaccine excipients, in single dose vials.

It is planned that a total of 100 subjects will receive the M01ZH09 vaccine in a bicarbonate solution containing 1.75% (w/v) sodium bicarbonate, 1.1% (w/v) ascorbic acid and 0.02% (w/v) aspartame. The solution is prepared from bicarbonate tablets using drinking water.

It is planned that a total of 50 subjects will receive placebo, consisting of the vaccine excipients in a bicarbonate solution containing 1.75% (w/v) sodium bicarbonate, 1.1% (w/v) ascorbic acid and 0.02% (w/v) aspartame. The solution is prepared from bicarbonate tablets using drinking water.

Subjects aged 5 to 10 years will receive the vaccine or placebo in 75 mL of bicarbonate solution. Subjects aged 11 to 14 years will receive the vaccine or placebo in 150 mL of bicarbonate solution

## **2.9 Compliance Statement**

This study is to be performed in compliance with this protocol, local and national guidelines and regulations and the following code of federal regulations;

- 21CFR 50 subpart B – Informed Consent of Human Subjects
- 21CFR54 – Financial Disclosure by Clinical Investigators
- 21CFR312.60 – General Responsibilities of Investigators
- 45CFR46 – Protection of Human Subjects
- Current ICH Guideline for Good Clinical Practice

Quality assurance systems and procedures will be implemented to assure the quality of every aspect of the study.

### **3 STUDY PURPOSE, OBJECTIVES AND ENDPOINTS**

#### **3.1 Purpose**

The purpose of the study is to determine the safety and immunogenicity of the oral vaccine M01ZH09 in healthy paediatric Vietnamese subjects. The clinical studies performed to date with M01ZH09 have assessed safety, tolerability and immunogenicity in adult subjects in the USA, UK and Viet Nam. Later in the clinical development of M01ZH09, Phase III field trials will be necessary in an area where typhoid fever is endemic. Potential areas for such a study exist in Viet Nam and Nepal. Field trials of a typhoid vaccine will involve children, as children under 10 years of age make up a significant proportion of the population that experience typhoid disease. The purpose of this study is to demonstrate immunogenicity and safety in a paediatric Vietnamese population prior to initiating field trials where it is anticipated that the youngest subjects that will be vaccinated will be 5 years of age.

#### **3.2 Objective**

To evaluate the safety and immunogenicity of M01ZH09 typhoid vaccine (oral live *S. typhi* (Ty2 *aroC* *ssaV*) ZH9) at a nominal dose of  $5 \times 10^9$  CFU in healthy paediatric subjects from Viet Nam.

#### **3.3 Safety Endpoints**

##### **3.3.1 Primary**

The proportion of subjects reporting SAEs attributed to the study medication.

##### **3.3.2 Secondary**

The proportion of subjects;

- Experiencing an elevated body temperature, of 38.5°C or greater, in the 14 days following dosing, attributed to study medication.
- Demonstrating persistent (after Day 7) faecal shedding of *S. typhi* (Ty2 *aroC* *ssaV*) ZH9.
- Withdrawn from the study due to adverse events, including bacteraemia, attributed to study medication.
- With clinically significant changes in laboratory parameters, from Day 0 to any time post dosing, which are attributed to study medication.

#### **3.4 Immunogenicity Endpoints**

Assessment of the immune response will be made by determining the proportion of subjects who;

- Develop a positive immune response\* to *S. typhi* LPS as assessed by an increase in *S. typhi* LPS specific IgG at either Day 14 or Day 28.
- Develop a positive immune response\* to *S. typhi* LPS as assessed by an increase *S. typhi* LPS specific IgA at either Day 7 or Day 14.

- At Day 7, have = 4 ASCs per  $10^6$  PBMC, secreting IgA specific for *S. typhi* LPS detected by ELISPOT assay

\*The definition of a 'positive immune response' will be determined following the completion of assay development.

## **4 STUDY DESIGN**

### **4.1 Summary of Study Design**

This is a placebo-controlled, parallel group, randomised, single-blind, single centre study. Subjects will be randomly allocated to one of two treatment groups and will receive either a single dose of M01ZH09 at a nominal dose of  $5 \times 10^9$  CFU or placebo. A total of 100 subjects will take M01ZH09 and 50 will take placebo.

### **4.2 Rationale for Study Design**

The study will be conducted following the principles of a double blind study, as per the accepted norm as the gold standard for these types of study. While this is the intent, perfect blinding cannot be guaranteed for a number of reasons (see Section 4.5, Blinding). The placebo serves as a measure of background adverse events and wild-type typhi immunogenicity markers. Allowing more children in the range 5-10 years of age will increase the data available in the age group to likely be employed for Phase III field trials.

### **4.3 Study Population**

The study will recruit 150 healthy paediatric Vietnamese subjects. Subjects will be of either gender and will be between 5 and 14 years of age, inclusive, who are willing to take part, whose parents or guardians give written permission and who meet all the inclusion and exclusion criteria.

At least 70% of the subjects in each group will be aged 5 to 10 years inclusive.

### **4.4 Rationale for Dose**

The purpose of this study is to investigate the safety and immunogenicity of the vaccine in a different age group to that tested to date. To achieve this it is essential to use a dose that is known to be immunogenic. In previous studies, the maximum dose administered ( $5 \times 10^9$  CFU) has been shown to be immunogenic. Lower doses investigated in previous studies were immunogenic in approximately 50% of the subjects. The safety profiles have been similar for all doses administered; hence, at the doses investigated, toxicity did not limit dosing. There is precedent for using the same dosage of live typhoid vaccine in children as adults. School children in the Vivotif (Ty21a) clinical trial in Chile received the same regimen as used for the licensed product in adults (Ferreccio et al., 1989). Moreover, Vivotif is licensed for use in the USA; it is indicated for immunisation of adults and children greater than 6 years of age using the same immunisation schedule. In line with other live vaccines, such as Stamaril (yellow fever) and Meruvax II (rubella), the same parenteral dose is given to children as it is to adults. For these reasons it has been determined that the appropriate dose for this study is a nominal dose of  $5 \times 10^9$  CFU of *S. typhi* (Ty2 aroC ssaV) ZH9.

### **4.5 Blinding**

Active vaccine and matching placebo will be packaged identically but with a unique sequential number. This number will enable identification of the contents in case of emergency when used

with the randomisation code break. Preparation of both active and placebo doses will be identical. Hence the investigator and his staff will be essentially blinded in that knowledge of the product supplied to the subjects will remain unknown. However, three areas remain where unintentional unblinding may occur.

1. The placebo and M01ZH09 solutions differ slightly in taste and aroma. Individual subjects will be unaware of any differences in dosing solutions and consequently will be blinded to their treatment in the study. The investigator may detect a difference between the products based on the aroma. A double observer design would reduce this risk but personnel with paediatric expertise at the site are limited, and a double observer design is unlikely to be possible.
2. Subjects will have stool samples taken for culturing and it is anticipated that subjects receiving M01ZH09 will shed *S. typhi* (Ty2 *aroC* *ssaV*) ZH9 in their stools. Results from the stool microbiology will therefore potentially unblind the investigator. It is intended to request that the Investigator does not review these microbiology reports for at least the first 14 days post dosing.
3. Subjects will have blood samples taken for the determination of IgG and IgA specific to *S. typhi*. Subjects that develop an immune response will clearly be identifiable as having received M01ZH09. For this reason it is intended to request that the Investigator does not review these immunology results for at least the first 14 days post dosing.

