### 6.2 Method of Administration of Each Dose

The method for the reconstitution and administration of the vaccine will be detailed in a separate document provided to the Pharmacist and Investigator.

Subjects will fast for at least 2 hours prior to taking the dose of medication and for 90 minutes after dosing (nothing to eat or drink, with the exception of water). The subject will remain at the Investigative site, under observation, for at least 90 minutes following dosing.

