## **6.5 Other Materials**

Emergent Product Development UK Ltd will provide syringes for use during reconstitution of the vaccine, and dosing containers.

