## **6.7 Compliance**

The study staff will administer the study medication and observe the subjects' compliance.

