### **8.1.4 Relationship to Study Product Assessment Definitions**

The Investigator will be requested to evaluate the relationship between the AE and the study medication according to the following scale:

- Probably: Good reason and sufficient documentation to assume a causal relationship
- Possibly: A causal relationship is conceivable and cannot be dismissed
- Unlikely: The event is most likely related to an aetiology other than the investigational product

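### Section 4.5 admits that the investigator may recognise the product by its aroma but sets no safeguard for that route, although the same investigator rates the severity and causality of adverse events

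*Protocol*

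**What the plan says.** Sections 4.1 and 4.2 describe a single-blind trial run on double-blind principles, and warn that blinding may be imperfect. Section 4.5 first calls the investigator and his staff essentially blinded, then lists three routes by which the blind may be lost. The first is the product itself: "The placebo and M01ZH09 solutions differ slightly in taste and aroma", and "The investigator may detect a difference between the products based on the aroma". One remedy is considered, a second observer, and set aside because "personnel with paediatric expertise at the site are limited, and a double observer design is unlikely to be possible".

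On handling of the dose, Section 6.2 says that the method of reconstitution and administration "will be detailed in a separate document provided to the Pharmacist and Investigator". Section 6.7 says "The study staff will administer the study medication and observe the subjects' compliance". Section 6.5 says that the sponsor "will provide syringes for use during reconstitution of the vaccine, and dosing containers", without describing the containers. Vials go to the site pharmacy (4.6), and a pharmacist keeps the accountability log (6.4).

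On assessment, Section 8.1.4 says "The Investigator will be requested to evaluate the relationship between the AE and the study medication", and 8.1.3 gives the Investigator the severity rating as well. The primary safety endpoint (3.3.1) is "The proportion of subjects reporting SAEs attributed to the study medication".

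**The concern.** Written rules for grading and attributing events are identical in the two arms, but they protect the comparison only if the person applying them does not know the arm. Exposure to the aroma would come on Day 0, before any post-dose event has been rated, so the later holds on stool and immunology reports cannot restore a blind already lost.

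At stake are the outcomes that depend on the Investigator's judgement of cause: attributed SAEs, fever and laboratory changes. Withdrawals for adverse events belong here too on the punctuation of 3.3.2; in Section 1 and 9.2.4.2 the word attributed can be read as applying to bacteraemia only. Section 1 plans between-group comparisons of attributed SAEs, symptomatic fever and laboratory changes. Relatedness also enters the dosing-suspension rules in 4.8.1. The review that follows a Table 1 trigger is by the Investigator and the sponsor's Medical Monitor, and 8.4 provides no safety committee. No independent blinded causality rating is described.

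**Working it through.** The plan states no figure on this point, so the main check is textual.

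**1. The three routes in 4.5, side by side**

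| Route | Earliest exposure | Safeguard in the text |
|---|---|---|
| Aroma of the solution | Day 0, at preparation and dosing | None; a double observer is considered and set aside |
| Stool microbiology | After dosing, once cultures are reported | Investigator asked not to review reports for at least 14 days |
| IgG and IgA results | After dosing, once assays are reported | Investigator asked not to review results for at least 14 days |

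The earliest route is the only one with no safeguard.

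**2. Does the stated reason fit the problem?** A double-observer design needs a second person able to assess children, so a shortage of paediatric expertise is a fair reason not to adopt one. Dissolving a tablet, adding a vial and handing over a container need no paediatric rating skills. The protocol already has a pharmacist and study staff, and the sponsor already supplies the containers. The shortage therefore does not rule out keeping the single assessor away from the open solution. The protocol does not name who reconstitutes the dose, does not exclude the rater from preparing or giving it, and does not say whether containers are lidded or opaque.

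**3. How large could the effect be?** This is an illustration only. Let the true event rate be q in both arms, and let attribution probabilities be a for vaccine and p for placebo if every dose were identified. Then

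spurious difference = q × (a − p).

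The values of q, a and p are assumptions, not protocol figures.

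| True event rate q | a = 60%, p = 40% | a = 70%, p = 30% |
|---|---|---|
| 2% | 0.02 × 0.20 = 0.4 points | 0.02 × 0.40 = 0.8 points |
| 10% | 0.10 × 0.20 = 2.0 points | 0.10 × 0.40 = 4.0 points |
| 30% | 0.30 × 0.20 = 6.0 points | 0.30 × 0.40 = 12.0 points |

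If only a share d of doses is identified, and attribution is otherwise equal in the two arms, each entry is multiplied by d. With 100 and 50 children (9.1), the 2% row at 70%/30% means an expected 100 × 0.014 = 1.4 attributed cases on vaccine and 50 × 0.006 = 0.3 on placebo. With even 50% attribution the figures would be 1.0 and 0.5. For a rare outcome such as attributed SAEs, the distortion is a fraction of one case per arm on average. For commoner judged events it can reach several percentage points.

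**The case against.** The strongest reply is that nothing is hidden or misstated. The trial is declared single-blind, 4.2 warns that blinding may be imperfect and refers to 4.5, and 4.5 calls the difference slight and detection possible. That stands. A reader might infer that every post-dose rating is unblinded; the text supports only a risk of it.

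Second, the separate preparation document under 6.2 is not available and may already divide preparation from assessment. That also stands. The fair statement is that the protocol itself does not specify the separation. Nor does 4.5 conclude that nothing can be done about aroma; it says only that one particular design is unlikely to be feasible.

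Third, much of the safety picture does not depend on attribution. Section 9.3 summarises all adverse events after vaccination, and also by severity, seriousness and relationship. Fever is defined by a temperature threshold (8.1.6), and laboratory severity for the suspension rules is numeric (Table 3). Faecal shedding needs no causality rating, and the IgG and IgA ELISAs are run by the sponsor (7.1). This confines the concern to judged outcomes but does not remove it, because the primary safety endpoint is one of them.

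Finally, a reader might put a false-positive rate on the leak. In MS01.07, 9 + 8 = 17 of 27 adults (63%) reported an adverse event. Assuming 63% in both arms, with attribution of 60% and 40%, the spurious difference is 0.63 × 0.20 = 12.6 points times the share of doses identified. Under a baseline attribution of 50%, the standard error is √(0.315 × 0.685 × (1/100 + 1/50)) ≈ 8 points, and a nominal 5% test would reject about 12% of the time at half the doses identified and about 35% at all. Those figures describe any attributed adverse event, which is not a listed endpoint, under assumed shifts. They do not carry over to attributed SAEs: no related SAE was seen in MS01.03 and no SAE in MS01.04 or MS01.07. Section 9.2.1 also describes the analyses as primarily estimation in an exploratory study, and 9.3 sets no safety hypothesis test.

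**Conclusion.** The point holds as a cheap improvement. Section 4.5 leaves the aroma route without a safeguard, for a reason that does not address it, while the Investigator rates severity and causality for a primary safety endpoint defined by attribution. The size cannot be derived from the document. On the assumptions shown it is under 1 percentage point for rare events and 6 to 12 points for judged events at a 30% rate, if every dose is identified, and it shrinks in proportion to the share identified.

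A reader might also infer that the existing pharmacist and containers could close the leak. The documents do not show this. The containers are undescribed, and the stool and immunology routes remain, held only by a request for at least 14 days. Separation and lids would reduce the risk. The ELISA immunogenicity results do not depend on causality ratings.

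**What to change.** - In 4.5, 6.2 and 6.7, state that the person who rates severity and causality for a child does not prepare or give that child's dose and is not beside the open solution.
- Name the pharmacist or other existing study staff as the people who prepare and give the dose, record that it was completed, and call the investigator, who stays available on site, for any reaction.
- In 6.5, specify lidded, opaque dosing containers.
- In 4.5, reconcile the statement that the investigator and staff are essentially blinded with item 1. Say that no second paediatric assessor is needed for this separation.
- If the separate preparation document already contains these steps, refer to them in the protocol.

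The cost is a few sentences, a matching change to the preparation instructions, and lids for about 150 containers. It needs no more subjects or visits and no second paediatrician. The downside is that the assessor does not directly see the child take the dose, so the record of completion must come from whoever gives it.
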